#### Text Message Delivery

SMS text messages will be delivered through an SMS text messaging service that enables scheduled sending. Low-reflection prompts, high-reflection prompts, reminder messages, and reminders to wear the Apple Watch and fill out the planning questionnaire will not be personalized with participants’ names or other identifiers (however, for low-reflection prompts, each participant will receive only the messages that they themselves wrote). SMS text messages will be sent from the same mobile phone number each time so that participants recognize it as coming from the study team. The participants’ responses to high-reflection prompts will be received by the same SMS text messaging service and associated with their mobile phone number so that their responses can be tracked and analyzed.

### Measures

Study data will include activity data as measured by Apple Watch (primary outcome) and self-report, questionnaires about affect and exercise, and video chat or telephone interview data about participant experience with the intervention. Questionnaires will be hosted on the Qualtrics platform and sent to participants via SMS text message.

#### Primary Outcome

The primary outcome for the microrandomized trial will be *calories burned*, as assessed by the Apple Watch, over the planned 4-hour exercise periods scheduled through the planning questionnaire. Apple Watch data will be collected through the MyDataHelps platform (CareEvolution, LLC), a secure platform for the collection of sensor (Apple Watch and Fitbit) and self-report data in health research. Participants will install the MyDataHelps app on their mobile phone. As calories burned can be reported by Apple Watch in discontinuous intervals, we will sum the calories burned over the 4-hour planned exercise period. When the intervals of reported calorie data cross the 4-hour planned exercise period boundary, we will assume that the calories burned are equally distributed across the reported interval and include only these calories in the 4-hour planned exercise period. Although Apple Watch’s calories burned measurement has moderate rather than high correlation with other energy expenditure measures [52], calories burned were selected as the primary outcome measure because it enables us to assess participants’ engagement in a greater variety of exercises compared with a more restrictive measure, such as steps. In this study, participants are instructed to perform any moderate to vigorous exercise they choose and to tell us what they plan to do in the planning questionnaire. Other data (described in the next subsection) will provide secondary records of the exercise performed for secondary analyses.

#### Exercise Data: Sensor and Self-Report Data

In addition to exercise being assessed via calories burned, it will also be assessed through several additional Apple Watch metrics, including active minutes, steps, and standing time. These metrics will also be collected through the MyDataHelps mobile app. As with calories burned, we will analyze step data and active minutes in the 4-hour planned exercise period.

On the days that participants plan to exercise, they will be asked to complete an exercise self-report questionnaire in the evening asking whether they exercised that day and, if so, how their activity compared with what they had planned; for example, was it shorter or longer in duration than they had planned? Participants will further be asked about their perceived exertion and affective state during and after exercise and, as a manipulation check, whether they received and read an SMS text message from the study team before exercise. If participants say they did not exercise, they will be asked why.

#### Affect Measures

The exercise self-report questionnaire will ask participants about their affective states during and after exercise, as well as expected postexercise affect for the next exercise session. In addition, at 3 points in the study (baseline, the 3-week check-in, and the end of the study), participants will be asked questions about their affective attitudes toward, during, and after exercise (Table 3).

#### Participant Experience

A closing survey will ask participants about their subjective perceptions of different aspects of the intervention. In addition, interviews will allow us to explore participant experience with the intervention and their perceptions of its impact on their behavior and attitudes.

### Participants

US residents with an iPhone and Apple Watch who are aged at least 18 years and have not been medically advised against physical activity are eligible to participate. Participants will be recruited through web-based channels such as email lists and relevant internet forums. They will be informed about the study and will give consent through a web-based questionnaire.

### Sample Size and Power

Sample size was calculated according to the methods published by Liao et al [43]. A microrandomized trial is an efficient trial design that enables causal inference with relatively small samples [42,43]. For this study, proximal treatment effect was estimated at 0.2, significance set at .05, and power set to 0.9. To power our study for the primary analysis (refer to the next subsection)—a contrast between no message and affective messages—availability was set to 0.7 to exclude reminder messages that are randomized at 30% probability. Given these assumptions, 89 participants are needed. We intend to recruit up to 120, allowing for dropouts.

### Data Analyses

#### Primary Analysis

Our primary interest is the average effect of the affective message intervention across time on calories burned during the planned exercise periods compared with no message being sent. To assess this effect, we will use the centered and weighted least squares method, a standard approach for analyzing microrandomized trial data that allows for robust causal inferences about treatment effects [53] and accounts for correlations in longitudinal data by nesting outcomes within participants. The covariates in our analysis will include time in study, the prior week’s proximal outcome, self-reported baseline activity levels, age, and gender.

#### Secondary and Exploratory Analyses

Additional analyses of the microrandomized trial data will investigate the time trend of the effect of affective messages (ie, the change in the effect of the affective messages over the duration of the study), the contrast between affective messages and reminder messages, and separate over-time and time-trend effects of low-reflection and high-reflection messages. In addition, we will investigate the intervention’s effect on other outcomes, such as step count and active minutes for the 4-hour planned exercise interval, as collected from the participants’ Apple Watches. These analyses, as in the case of the primary analysis, will all be conducted using the centered and weighted least squares method.

In addition to the microrandomized trial analyses, we will conduct a number of exploratory analyses of the affective measure data. We will examine potential changes in the anticipated postexercise affect by investigating changes in pre- and postintervention ratings on the Feeling Scale [27]. Exploratory analyses will include an investigation of changes in other affective measures used and the role of potential moderating factors such as baseline activity level, planned exercise intensity, and exercise intensity on postexercise affective state predictions. In addition to these quantitative analyses, we will thematically analyze interview data in accordance with the principles described in the study by Braun and Clarke [54]. After transcribing the interviews, we will use an iterative inductive approach to explore themes in the data around participants’ underlying needs and the impact the intervention had on their lives. We will triangulate interview responses with observed participant behavior and responses to the closing questionnaire to get a full picture of participant experience with the intervention and insight into appropriate outcome metrics for future iterations.

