**Methods:**

A total of 120 individuals will be enrolled in a 9-week microrandomized trial testing affective messages that remind users about feeling good after exercise (40% probability), control reminders (30% probability), or no message (30% probability). Two types of affective SMS text messages will be deployed: one requiring a response and the other in a read-only format. Participants will write the read-only messages themselves to ensure that the messages accurately reflect the participants’ anticipated postexercise affective state. Affective attitudes toward exercise and intrinsic motivation for exercise will be measured at the beginning and end of the study. The weighted and centered least squares method will be used to analyze the effect of delivering the intervention versus not on calories burned over 4 hours around the time of the planned activity, measured by the Apple Watch. Secondary analyses will include the effect of the intervention on step count and active minutes, as well as an investigation of the effects of the intervention on affective attitudes toward exercise and intrinsic motivation for exercise. Participants will be interviewed to gain qualitative insights into intervention impact and acceptability.

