**Exercise self-report information (after every planned exercise session)**			
	Exercise self-report; 18	Exercise self-report questionnaire	Did you do any exercise today?; Yes, No (conditional) Was the exercise you did today the same as what you originally planned, or different?; Exactly what I had planned; Different from what I had planned; I’m not sure, I can’t remember what I planned (conditional) What exercise did you do today?; free text (conditional) Please let us know why exercise didn’t fit into your day today (conditional) How did the exercise you did differ from what you had planned?; Pushed myself harder; Scaled back my activity; Did the activity in a different place or with different company; Did a different activity; Did the activity at a very different time than I had planned; Other difference
	Exercise exertion; 18	Exercise self-report questionnaire	Thinking back on your physical activity session today, rate your overall level of exertion during it. This feeling should reflect how heavy and strenuous the exercise felt to you, combining all sensations and feelings of physical stress, effort, and fatigue. Focus on your total feeling of exertion, not any one specific factor; 10-point scale ranging from 1=rest (no exertion at all) to 10=maximal effort (I was completely exhausted and it felt almost impossible to keep going)
	Affect during exercise (recollected); 18	Exercise self-report questionnaire	While you were doing your exercise session today, how did you feel overall?; free text Rate how good or bad you felt overall while you were doing your exercise; Feeling Scale [27]
	Postexercise affect (recollected); 18	Exercise self-report questionnaire	After you did your exercise session today, how did you feel overall?; free text Rate how good or bad you felt after your exercise session; Feeling Scale [27]
	Anticipated postexercise affect (next session); 19	Exercise self-report questionnaire and planning questionnaire (with baseline questions)	How do you expect to feel after your next exercise session? Select the number that best represents how good or bad you expect to feel; Feeling Scale [27]
	Unplanned exercise; 18	Exercise self-report questionnaire	Have you done any unplanned exercise since your last planned exercise session (not today’s)?; Yes, No, This was my first planned exercise session for this study (conditional) What was the unplanned exercise you did?; free text

^a^SRQ-E: Exercise Self-Regulation Questionnaire.

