#### Study Procedures Overview

At enrollment, we will ask participants to write their low-reflection prompts and to self-report demographic and baseline activity–level information. In addition, we will assess participants’ anticipated affect for exercise, their affective association with exercise, and their overall enjoyment of exercise. On top of these measures, we will ask participants to complete the Exercise Self-Regulation Questionnaire [44,45] to measure their intrinsic motivation for exercise and the Physical Activity Enjoyment Scale (PACES-8) [46] to measure their enjoyment of exercise.

For the next 9 weeks, at the start of each week, participants will be asked to list 2 time intervals during which they plan to exercise in the coming week. At the start of each planned exercise time interval, participants will be randomized to receive an affective SMS text message (intervention), a control reminder message, or no message, and at the end of the day, they will be asked to report their actual exercise details (refer to *Exercise Data: Sensor and Self-Report Data* section). Thus, each participant will be randomized to receive an intervention, a control reminder message, or no message 2 times each week.

At the close of the 9-week period, participants will be sent a closing questionnaire that contains questions about their experience with the intervention, all items from the Exercise Self-Regulation Questionnaire and the PACES-8, and the same questions about affect related to exercise that were assessed at baseline.

After the 9-week study period, a subset of participants will be interviewed to gather in-depth data about their experience with the intervention and their perceptions of its impact on their attitudes toward exercise and on exercise behavior. We plan to stratify our interview sample based on participant characteristics such as exercise frequency and participant responses to the closing questionnaire, low-reflection sentences, and responses to high-reflection prompts.

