## Discussion

### Implications and Limitations

Researchers have increasingly highlighted the potential of affective and nonconscious motivators to influence exercise behavior [21,55]. Past work has demonstrated the ability of the manipulations of expected postexercise affect to have an impact on during-exercise affect, postexercise affect, and behavioral intention to exercise [35,36]. Our study investigates the impact of repeating that manipulation in a format that is at once highly personalized and highly scalable and that can be carried forward through time at key decision points for exercise behavior. In addition, we extend prior work by examining the impact of the manipulations of expectations of postexercise affect not only on behavioral intentions but also on actual exercise behavior. The findings will elucidate the influence of this intervention over time on both immediate exercise behavior and overall affective attitudes toward exercise. Given recent findings that affective attitudes toward exercise on a particular day have an impact on exercise behavior over and above affective attitudes toward exercise in general [56], there is high potential for an mHealth intervention manipulating affective attitudes in the moment to influence physical activity. As our study design includes qualitative data, we will also gain insight into participants’ *experience* with the intervention, yielding findings that can shape the design of other systems and uncover unforeseen complications.

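### Uncontrolled pre-post change cannot show the promised intervention effects on affect; the evening ratings allow a randomized contrast, but only of a same-day effect

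*Protocol article*

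**What the plan says.** Under Secondary and Exploratory Analyses, weighted and centered least squares is assigned to the message contrasts and time trends and to further outcomes "such as step count and active minutes for the 4-hour planned exercise interval, as collected from the participants’ Apple Watches". Affect is then taken up separately: "In addition to the microrandomized trial analyses, we will conduct a number of exploratory analyses of the affective measure data". The method for the main affective construct, anticipated postexercise affect, is "investigating changes in pre- and postintervention ratings on the Feeling Scale". The other affective measures are also to be looked at as changes. No comparator is named.

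The stated aims are causal. The abstract lists among the secondary analyses "an investigation of the effects of the intervention on affective attitudes toward exercise and intrinsic motivation for exercise". Study Contribution promises findings on what the manipulation does to actual postexercise affect and other attitude measures. Implications and Limitations says: "The findings will elucidate the influence of this intervention over time on both immediate exercise behavior and overall affective attitudes toward exercise". The same section says the analyses will address the impact of the messaging beyond whatever planning and self-monitoring contribute.

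Table 3 shows that Feeling Scale ratings are also collected in the self-report questionnaire after each planned session. One is the recollected postexercise rating (18 times). Another is the item "How do you expect to feel after your next exercise session" (19 times, one of them in a planning questionnaire). Study Procedures Overview places this questionnaire at the end of the day of each randomized session.

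**The concern.** A change from before to after the nine weeks combines the affective messages with everything else that happens to a participant: weekly planning, reminders, self-report, watch feedback, repeated testing, season, regression to the mean, and selective return of the closing questionnaire. The protocol recognizes part of this. Its Reminder Message section grants that planning may change behavior by itself and adds a randomized reminder to control for it. The pre-post affect analysis uses no such control.

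What is at stake is the conclusion on mechanism. The Discussion bases next steps on whether attitudes, behavior or only one of them moved, and a shift caused by something other than the messages would misdirect that decision. Meanwhile, a rating of the main affective construct is collected after every randomization and no randomized contrast is stated for it.

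**Working it through.** **1. Is there an unexposed group?** Inputs (Randomization Overview and Randomization Procedure): 18 decision points; probabilities 0.4 affective, 0.3 reminder, 0.3 none. Draws are treated as independent.
- No affective message in 18 draws: 0.6^18 ≈ 0.0001.
- All three conditions at least once: 1 − (0.6^18 + 0.7^18 + 0.7^18) + (0.3^18 + 0.3^18 + 0.4^18) ≈ 0.997.
- Affective messages per participant: mean 18 × 0.4 = 7.2; SD √(18 × 0.4 × 0.6) ≈ 2.1; 5th to 95th percentile 4 to 11.

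Participants who skip planning questionnaires receive fewer messages, but they select themselves and are not a control group.

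**2. What could a pre-post test show if the messages did nothing?** The plan names no test, so this is an illustration: two-sided 5% paired t test, noncentrality δ√N, where δ is background drift in SDs of change. The drift sizes are assumptions, and all N are taken to return the closing questionnaire.

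| Drift δ | Significant, N = 89 | Significant, N = 120 |
|---|---|---|
| 0.1 | 15% | 19% |
| 0.2 | 46% | 58% |
| 0.3 | 80% | 90% |

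Drift common to all conditions does not bias a session-level randomized contrast.

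**3. The plan's own sample size.** Inputs (Sample Size and Power): effect 0.2, alpha 0.05, power 0.9, availability 0.7, 89 participants. Test: noncentral F with one effect parameter and noncentrality N × d² × T × τ × ρ(1 − ρ), T = 18, constant effect.
- ρ = 0.4: 89 × 0.04 × 18 × 0.7 × 0.24 = 10.77, power 0.901. The required N is 89, as stated.
- ρ = 0.4/0.7 = 0.571, the chance of an affective message once reminders are set aside: required N is 88.

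**4. The same contrast on the evening rating (affective vs no message).** ρ = 0.571, with the noncentrality multiplied by the share of ratings returned. For N = 89 and full return it is 89 × 0.04 × 18 × 0.7 × 0.245 = 10.99. The effect of 0.2 for affect and the return rates are assumptions; the article gives neither.

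| Ratings returned | Power, N = 89 | Power, N = 120 |
|---|---|---|
| 100% | 0.906 | 0.968 |
| 80% | 0.834 | 0.927 |
| 60% | 0.719 | 0.841 |
| 40% | 0.545 | 0.675 |

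The smallest effect detectable with 80% power runs from 0.171 (all returned) to 0.270 (40% returned) at N = 89, and from 0.147 to 0.232 at N = 120.

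**5. What is the pre value for anticipated affect?** The places that describe it do not agree:
- Study Procedures Overview says anticipated affect is assessed at enrollment.
- Table 3's pre- and postintervention block has no such Feeling Scale item. It asks how participants typically feel after exercise.
- Table 3 puts the one rating outside the self-report questionnaire in a planning questionnaire labelled as carrying baseline questions.
- Textbox 1 sends that version once, midway through the study.
- Affect Measures gives three time points for affective attitudes (baseline, a three-week check-in and the end), whereas Table 3 gives two for the attitude items.

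**The case against.** The strongest defence is status. The section on analyses calls these exploratory, names no test or threshold, and leaves the confirmatory question on calories untouched. An article also need not list every exploratory model. This limits the weight of the point but does not remove it: the method that is stated is pre-post change, the abstract places attitude effects among the secondary analyses, and neither label turns an uncontrolled change into an intervention effect.

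Several stronger readings are tempting, and the documents do not support them.
- *The session ratings would give a controlled estimate of overall attitudes.* They would not. General attitude, affective association, regret, pride, SRQ-E and PACES-8 are scheduled at enrollment and closing only in Table 3. A session contrast estimates the same-day effect of one message, not a nine-week effect.
- *The evening rating isolates the mechanism.* It is given after any exercise and concerns the next session, which has its own assignment. It reflects the day's experience as well as the message.
- *The session-level affect data are ignored.* The plan mentions moderators of postexercise affect predictions, including planned and actual exercise intensity, so some use of these data is likely. What is absent is a randomized contrast.
- *Power of 0.90 is available.* That holds only with full response and an effect of 0.2 borrowed from the calorie calculation. The Missingness section itself expects gaps.
- *Baseline ratings are primed by message writing.* Study Procedures Overview begins "At enrollment, we will ask participants to write their low-reflection prompts" and mentions the affective items afterward, but this is narrative and does not fix the order of the form. Priming would tend to shrink an apparent improvement. With 57 already enrolled by the end of July 2023, reordering would create two versions of baseline.

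**Conclusion.** The point holds in a limited form. Pre-post change without a concurrent control cannot support the effects on affect that the article announces. For anticipated postexercise affect, a randomized and nearly free alternative exists in data already being collected. For the measures taken only at enrollment and closing it does not, and only the wording can be put right. The primary analysis stands.

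The size of the problem depends on drift, which the article does not give; under the assumed 0.1 to 0.3 SD, false attribution at 89 to 120 participants ranges from 15% to 90%. The value of the alternative depends on response: for an assumed effect of 0.2 at 89 participants, about 0.91 with full return, falling to 0.72 at 60%. The anticipated-affect item is the cleaner outcome because Table 3 does not make it conditional on exercise. Recalled postexercise affect exists only for those who exercised, which the message may itself influence, so randomization does not fully protect that comparison.

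**What to change.** 1. Add the evening Feeling Scale rating of anticipated postexercise affect as a secondary or exploratory proximal outcome in the same weighted and centered least squares model, affective vs no message and affective vs reminder. Describe it as the same-day effect of one message.
2. Report questionnaire response by condition, because the reminder text asks participants to complete the exercise-day questionnaire and may raise response in that condition.
3. Analyze recalled postexercise affect in the same way only as a contrast conditional on having exercised, and label it so.
4. Report enrollment-to-close changes in general attitude, affective association, anticipated regret and pride, SRQ-E and PACES-8 as descriptive. Align the wording of the abstract, Study Contribution and Implications and Limitations with this.
5. State which rating is the pre value for anticipated affect, and reconcile Study Procedures Overview, Textbox 1, Table 3 and Affect Measures.

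The cost is one extra model on data already collected, plus wording. The downside is a proximal rather than a cumulative estimand. The enrollment form should stay as it is.
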